**Methods:**

This assessor-blinded, 2-arm, randomized waitlist-controlled trial enrolled 132 individuals with PD and balance impairment, randomized to either the MY-PACE group (n=66, 50%) or the control group receiving routine outpatient care (n=66, 50%). The MY-PACE group will complete a 12-week, Zoom-delivered program incorporating mindfulness, yoga, and mindful walking practices. The control group will receive the intervention after study completion. The primary outcome is functional balance, as measured by the Berg Balance Scale. Secondary outcomes include functional mobility, gait patterns, balance confidence, freezing of gait severity, motor symptoms, anxiety and depressive symptoms, cognitive function, mindfulness, health-related quality of life, and fall incidence. Assessments will occur at baseline, 3 months (T1), and 6 months (T2). Data will be analyzed using linear mixed-effects models under the intention-to-treat principle.

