### Aims and Hypotheses

This study aims to do the following:

Examine the effects of MY‑PACE, compared with usual care, on functional balance (primary outcome) and secondary outcomes, including functional mobility, balance confidence, freezing of gait (FOG) severity, motor symptoms, anxiety and depressive symptoms, cognitive function, mindfulness, HRQOL, and the incidence of falls over a 6‑month period in individuals with PDExplore participants’ experiences with MY‑PACE, including their practice of mindfulness yoga and factors influencing motivation, acceptability, and integration into daily life

It is hypothesized that participants with PD who receive the MY‑PACE intervention will demonstrate significantly greater improvements in functional balance at postintervention follow-up (T1) and at the 6‑month follow‑up (T2) compared with those receiving usual care. In addition, it is hypothesized that participants in the MY‑PACE group will show greater positive changes in secondary physical, psychological, and cognitive outcomes relative to the control group across the same time points.

The exploratory research question is as follows: What are participants’ experiences of using mindfulness yoga as a lifestyle intervention for balance management, particularly regarding perceived effects, perceived mechanisms of action (ie, how and why mindfulness may or may not work), and contextual factors influencing motivation, acceptability, and real‑life practice?

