### Sample Size Calculation

Taking functional balance as the primary outcome, a meta‑analysis in individuals with PD reported a pooled mean difference of 3.64 (95% CI 2.06-5.22) points for resistance and balance training compared with control, corresponding to an estimated standardized effect size of Cohen *d*=0.66 [25], while a meta-analysis of cognitive-motor training in PD reported a standardized mean difference of 0.58 for balance outcomes compared with active or passive controls [26]. As this study will compare internally cued motor training with usual care, a conservative moderate effect size of 0.55 is assumed for the primary outcome. Using G*Power (version 3.1) for a 2‑arm parallel randomized controlled trial with a 2‑sided significance level of 0.05 and 80% power, 110 participants were required to detect an effect size of 0.55. Allowing for an anticipated attrition rate of 20%, a total sample size of 132 participants (66 per group) was recruited.

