### Procedure

Participants were recruited from local outpatient clinics and community organizations serving individuals with PD, including the Hong Kong Parkinson’s Disease Foundation, the Hong Kong Parkinson’s Disease Association, and the Community Rehabilitation Network. Study information and promotional materials were disseminated through online platforms and organizational networks. Potential participants were contacted by telephone or WhatsApp (Meta Platforms Inc) and screened for eligibility. Eligible individuals received a detailed explanation of the study via videoconference. Written informed consent was obtained in person prior to data collection. Following consent, baseline demographic and clinical assessments were conducted. All outcome assessments were performed during the participants’ self-reported medication “on” state to minimize the influence of motor fluctuations. Assessments were administered by trained research personnel who were blinded to group allocation. Participants were then randomly assigned in a 1:1 ratio to either the MY-PACE group (mindfulness-based, internally cued motor training) or the usual care group using a computer-generated randomization sequence. The allocation sequence was prepared by a researcher not involved in recruitment, intervention delivery, or outcome assessment. Group allocation was communicated to participants by an independent staff member to ensure allocation concealment. All outcome assessors remained blinded to group assignment throughout the study period.

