#### Secondary Outcomes

Functional mobility is assessed using a validated smartphone-based instrumental 3-meter Timed-Up-and-Go (TUG) test [17] via the US Food and Drug Administration–approved Mon4t Clinic (Montfort Brain Monitor Ltd) application [29]. A designated device is attached to the participant’s sternum using a flexible strap. Participants are instructed to sit on a chair with their hips positioned fully against the back of the seat. When the test starts, a countdown is heard, followed by an auditory and vibratory start cue. Participants are instructed to stand up, walk for 3 meters, turn around, walk back to the chair, and sit down. The total test time is recorded.

Gait patterns are assessed using a validated smartphone‑based 5‑meter instrumented TUG test via the Food and Drug Administration–approved Mon4t Clinic application. The device is positioned at the sternum as previously described. Participants complete 3 conditions: (1) a standard 5‑meter TUG test, in which they rise from a chair, walk 5 meters, turn, return, and sit down; (2) an obstacle 5‑meter TUG test, during which they walk 5 meters between 2 chairs spaced 24 inches apart before turning and returning to sit; and (3) a dual‑task 5‑meter TUG test. For the dual‑task condition, participants perform the 5‑meter TUG test while simultaneously completing a cognitive task involving serial subtraction performed continuously until the test is completed. Objective gait parameters, including step length, cadence, gait velocity, step-to-step variability, and postural sway, are extracted from the application.

Perceived balance confidence is measured in both medical “on” and “off” states using the Chinese version of the Activities‑Specific Balance Confidence Scale [30], a validated and reliable 16‑item instrument that evaluates individuals’ confidence in performing various indoor and outdoor activities. Each item is rated from 0% (no confidence) to 100% (complete confidence). Higher total scores indicate greater balance confidence.

Subjective experiences of FOG are assessed using the Chinese version of the FOG-Questionnaire [31]. The FOG‑Questionnaire consists of 6 items evaluating the severity and impact of freezing episodes on gait. Each item is rated on a 5‑point scale from 0 (absence of symptoms) to 4 (most severe), yielding a total score ranging from 0 to 24. Higher scores indicate more severe FOG.

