### Data Analysis

Data analysis will be performed using SPSS (version 28.0.1; IBM Corp) software following the intention-to-treat approach. Descriptive statistics will be used to summarize the sociodemographic characteristics and clinical background of all participants. The homogeneity of baseline characteristics between the 2 groups will be tested by the Pearson chi-squared test or Fisher exact test, as appropriate. Linear mixed-effect models will be used to assess the intervention effects on the primary and secondary outcomes, with time (as a continuous variable), group, and the group-by-time interaction included as independent variables. Linear contrasts will be used to obtain between-group differences. The normality of the residuals and random effects will be assessed using normal probability plots. Missing values will not be replaced because mixed-effect models can accommodate participants with at least 1 outcome measurement [37]. A 5% level of significance will be adopted, with all significance tests being 2-sided.

For the qualitative data, all audio-taped interviews will be transcribed verbatim and managed by NVivo (version 12.0; Lumivero LLC). Two experienced qualitative researchers will carefully and inductively review the transcripts. A 5-step thematic analysis will be adopted [38]. The coded units will be sorted into categories and subcategories and analyzed to identify recurrent themes and patterns. This qualitative data will enhance the interpretation of the quantitative findings and help identify the strengths and weaknesses of the intervention being tested. An audit trail will be maintained to ensure data credibility. The coded data will be compared to identify discrepancies, and any disagreements will be resolved through discussion.

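### The plan does not fix which Berg Balance Scale (BBS) contrast decides success: T1 and T2 are both hypothesised, but the sample size covers one comparison with no visit named

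*Protocol article*

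**What the plan says.** The Abstract (Methods) names a single primary outcome: "The primary outcome is functional balance, as measured by the Berg Balance Scale". Neither it nor the Primary Outcome section names a visit.

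Aims and Hypotheses expects significantly "greater improvements in functional balance at postintervention follow-up (T1) and at the" 6-month visit (T2), so two visits enter the primary hypothesis.

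Sample Size Calculation states that "a conservative moderate effect size of 0.55 is assumed for the primary outcome", again without a visit. The requirement reads "sided significance level of 0.05 and 80% power, 110 participants were required to detect an effect size of 0.55" and is then raised for attrition: "Allowing for an anticipated attrition rate of 20%, a total sample size of 132 participants (66 per group) was recruited".

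Data Analysis fits a linear mixed-effects model with group, continuous time and their interaction. It takes between-group differences from linear contrasts that it does not specify. On error control it says only: "A 5% level of significance will be adopted, with all significance tests being 2-sided".

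The Results section adds that the article reflects the original design and analysis plan, and that no outcome data have been analysed.

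**The concern.** A primary outcome is fully defined only when its visit and contrast are fixed. At least three BBS tests fit this text: the group difference at T1, the group difference at T2, and the group-by-time slope. The article does not say which one decides, or whether T1 and T2 are alternatives or joint requirements.

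The two-visit readings carry different risks, and neither matches the sample size. If either visit is enough, there are two chances at 5% each. If both are needed, the 80% power planned for one comparison does not apply to the pair. With the rule open, it could be settled after the results are known.

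**Working it through.** **Inputs.** From the article: two-sided alpha 0.05, power 80%, effect size 0.55, 110 evaluable, 1:1 allocation (55 per arm), time continuous, visits at about 0, 3 and 6 months. Not in the article and therefore assumed: the correlation between visits, taken over 0.5 to 0.9.

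**1. The plan's own figure.** A two-sample t-test at effect size 0.55, two-sided 0.05 and 80% power needs 53 per arm, 106 in total. The stated 110 gives 81.6% power. The stated figure is thus slightly more than a single full-alpha comparison needs, with no alpha split. Had alpha been halved to 0.025 for each of two visits, 65 per arm (130 evaluable) would be needed, and 110 would give 73% power.

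**2. Either visit suffices, visits estimated separately.** The type I error is 1 − P(|Z1| < 1.96 and |Z2| < 1.96), where Z1 and Z2 are standard normal with correlation r.

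| r | type I error |
|---|---|
| 0.5 | 9.1% |
| 0.7 | 8.3% |
| 0.8 | 7.8% |
| 0.9 | 7.0% |

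The ceiling, at r = 0, is 1 − 0.95² = 9.75%.

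**3. Either visit suffices, stated linear-time model.** Here the group difference at month t is a + b·t, so the visits share two parameters.

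- *Difference in change from baseline.* At T1 this is 3b and at T2 it is 6b. Both have the same test statistic and p-value, so the error is 5.0%.
- *Difference at each visit, a + 3b and a + 6b.* Assume equal within-person correlation of 0.5 across the three assessments. Up to a common factor, var(a) = 0.9167, cov(a, b) = −0.0833 and var(b) = 0.0278.
  - Variance at T1: 0.9167 − 6 × 0.0833 + 9 × 0.0278 = 0.667.
  - Variance at T2: 0.9167 − 12 × 0.0833 + 36 × 0.0278 = 0.917.
  - Covariance: 0.9167 − 9 × 0.0833 + 18 × 0.0278 = 0.667.
  - Correlation: 0.667 / √(0.667 × 0.917) = 0.85, so the error is 7.4%.
  - With within-person correlation 0.9, the contrasts correlate at 0.97 and the error is 6.1%.

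**4. Both visits required.** The type I error is at most 5%. For power, take the effect as 0.55 at both visits and 55 per arm. The expected test statistic is 0.55 × √(55/2) = 2.884, so power at one visit is Φ(2.884 − 1.960) = Φ(0.924) = 82.2% by the normal approximation. Joint power is P(Z1 < 0.924 and Z2 < 0.924).

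| r | joint power |
|---|---|
| 0.5 | 72% |
| 0.7 | 74% |
| 0.9 | 78% |

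Starting from the t-test power of 81.6% instead, these become 71%, 73% and 77%. If the effect fades by T2, joint power is lower still.

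**The case against.** **The word joining the visits is a conjunction.** Read literally, the hypothesis asks for T1 and T2 together, and then nothing is inflated. That stands for the type I error. It does not rescue the plan, because the sample size does not deliver 80% power for both (step 4).

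**The stated model has one interaction.** If the test is the slope, there is one p-value and the error is 5.0%. This also stands, and it keeps the inflation modest under the model as written. But the article follows the model with unspecified contrasts and a hypothesis at two visits, and it never says that the slope decides.

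**A separate analysis plan may settle it.** It may. However, the visit belongs to the definition of the primary outcome, and the article presents itself as reflecting the prespecified plan. If an existing plan names the contrast, quoting it closes the point.

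**A stronger reading to avoid.** A reader might infer that the many secondary measures, all at 5%, make a false positive claim somewhere in the trial nearly certain. The documents do not support that. They give no count of secondary tests. On gait they say "Objective gait parameters, including step length, cadence, gait velocity, step-to-step variability, and postural sway, are extracted from the application", not that every parameter is tested in every walking condition at every visit. Near-certainty would also need roughly independent tests, whereas these measures come from the same people at the same visits. The outcomes are already labelled secondary, so testing them unadjusted does not raise the primary error, and any adjustment is commonly left to an analysis plan.

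**Conclusion.** The point holds for the primary outcome: the article does not fix which BBS contrast decides success.

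- *Either visit suffices:* type I error of about 7.0% to 9.1% with separately estimated visits, or 6.1% to 7.4% for visit-specific group differences under the linear-time model.
- *Change contrasts in that model:* 5.0%, because both are the same slope test.
- *Both visits required:* at most 5%, with power of about 72% to 78% against the stated 80%.

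These ranges rest on an assumed correlation of 0.5 to 0.9, equal within-person correlation for the linear-model figures, and, for power, an effect of 0.55 at both visits with 110 evaluable. The inflation is modest. The point should still be settled because the rule defines a positive trial, and it can be settled blind to results while no outcome data have been analysed. The documents do not support a claim about the trial-wide error across secondary outcomes.

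**What to change.** Before any outcome analysis, record in a dated plan:

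1. One confirmatory contrast, for example the baseline-adjusted BBS group difference at T1, tested at two-sided 5%.
2. Visit as a categorical factor, so that T1 and T2 are estimated separately. Under linear time the two change contrasts share a p-value, and testing them in order would mean nothing.
3. T2 tested at two-sided 5% only if T1 is significant. This fixed sequence holds the error over both visits at 5% without splitting alpha.
4. Secondary outcomes labelled supportive and reported as estimates with 95% confidence intervals.

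The choice of T1 is an example. The sample size names no visit, so the investigators should choose the one that carries their main claim.

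The cost is small. N is unchanged, because the calculation already covers one comparison at the full 5%. The model does change, from linear to categorical time, so this is more than wording. The downside is that a T2 benefit cannot be claimed alone if T1 fails.

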## Results

Ethics approval was obtained on September 18, 2019. A small feasibility study (n=10) was conducted between May and June 2020 to inform the grant application for a full randomized controlled trial [39]. The study was subsequently funded by the Early Career Scheme 2021-2022 of the Research Grants Council, Hong Kong, with a funding period from January 1, 2022, to December 31, 2025. Prospective clinical trial registration was completed on December 10, 2021, prior to the start of recruitment in April 2022. As of manuscript submission, 132 participants have been enrolled. No outcome data analyses have been conducted to date. The submitted protocol reflects the original prespecified study design and statistical analysis plan. The trial results are expected to be published in 2026.

## Discussion

### Overview of the Study

PD is a progressive and irreversible neurodegenerative disorder affecting both motor and psycho‑cognitive function. Among its most disabling manifestations, functional balance impairment substantially contributes to falls, injuries, loss of independence, institutionalization, and mortality [4]. Despite its clinical importance, postural instability remains inadequately managed, particularly given the limited responsiveness of balance dysfunction to dopaminergic therapy. Therefore, there is a critical need for complementary, nonpharmacological strategies for functional balance rehabilitation.

Increasing evidence suggests that balance impairment in PD reflects disrupted integration among motor, attentional, and emotional processes rather than a purely motor deficit [4,8,9]. However, current rehabilitation guidelines continue to prioritize professionally led, externally cued exercise programs to improve gait and balance [11]. Rhythmic auditory stimulation and other cueing strategies are designed to facilitate movement by recruiting premotor cortical regions to compensate for basal ganglia dysfunction [12,13]. Although these approaches produce short-term improvements, their effects often diminish once external cues are withdrawn [14], raising concerns about long-term sustainability. Moreover, therapist‑dependent models are resource‑intensive and challenging to implement as continuous, real‑world support. Most externally cued interventions primarily target motor performance, with comparatively limited emphasis on modifiable nonmotor contributors, such as awareness training and anxiety management—factors that may underlie inconsistent translation of gains achieved in a structured setting into durable functional improvements.

The MY‑PACE program was designed to close critical gaps in PD rehabilitation by uniting mindfulness‑based attentional training with balance‑specific motor exercise within a whole‑person, person‑centered framework. Mindfulness practice cultivates present‑moment awareness and a nonjudgmental attentional stance, processes associated with enhanced attentional control and emotional regulation [16]. These processes may strengthen top‑down regulation of movement and emotional responses, allowing mindfulness techniques to function as internal cueing strategies that support intentional movement control, coordination, and postural alignment. In parallel, structured yoga‑based practice progressively trains balance, mobility, and mind-body coordination. Through this integrated approach, MY‑PACE engages motor, cognitive, and emotional domains that are foundational to functional performance and lived well‑being in PD. This trial evaluates a home‑based, interactive online delivery of MY‑PACE using a rigorous randomized controlled design. Effectiveness is tested with the BBS (primary outcome) and complemented by measures of mobility, psycho‑cognitive well‑being, and HRQOL. The repeated‑measures design, combined with participants’ experiential feedback, enables a comprehensive whole‑person evaluation of both impact and acceptability.

This study also tests a pragmatic tele‑rehabilitation model built for real‑world adoption. Traditional center‑based programs are constrained by transportation, cost, caregiver availability, and mobility limitations. Live‑streamed group sessions preserve structured guidance, peer connection, and real‑time feedback while markedly expanding reach. Daily self‑practice (audio‑guided mindful walking) embeds internally cued strategies into everyday contexts, increasing ecological validity and supporting sustained self‑management. By simultaneously targeting motor performance and key nonmotor drivers—especially attentional regulation and anxiety—MY‑PACE addresses the multidimensional nature of balance and mobility dysfunction in PD. If effective, this mindfulness‑based lifestyle program may be readily implementable within community rehabilitation services in Hong Kong and scalable across diverse health care systems. Findings from this trial can shape complementary rehabilitation pathways, advance priorities in fall prevention and mobility preservation, and inform chronic disease adaptation strategies. More broadly, this work contributes to accessible, community‑based, compassion‑focused models of PD care that align clinical benefits with patient values and everyday life.

### Limitations

Several limitations should be acknowledged. Despite using diverse recruitment strategies across clinical and community settings, participants who enrolled may have been more socially active, motivated, or technologically competent, introducing potential selection bias and limiting generalizability to individuals who are less engaged or more functionally impaired. Blinding of participants is not feasible because of the behavioral nature of the intervention, which introduces potential risks of performance and expectancy bias. To mitigate these effects, participants will not be informed of specific study hypotheses or detailed intervention content, the informed consent process will adhere to the principle of equipoise, and participants will be reminded not to disclose group allocation to outcome assessors to preserve assessor blinding. Importantly, the primary outcome (BBS) and several secondary mobility outcomes (eg, instrumented TUG tests and gait parameters) are performance-based and evaluated by blinded assessors or objectively quantified using instrumented measures, which may reduce susceptibility to expectation effects. Nevertheless, treatment expectancy and perceived intervention credibility are not formally assessed, limiting the ability to directly quantify potential expectancy influences. Incorporating validated measures of treatment expectancy and credibility in future studies may further strengthen the causal interpretation of between-group differences. Falls will be collected through monthly self-report and may therefore be subject to recall bias, despite the use of structured follow-up procedures and a standardized fall definition. Attrition is another methodological concern, as completion of 12 intervention sessions and 3 assessment time points may impose a participation burden. To enhance retention, flexible scheduling will be offered where feasible, control group participants will be offered the tested yoga intervention after completing follow-up assessments and modest financial incentives.

